# Efficacy and Safety of Kanggan Mixture for Influenza: Protocol for a Multicenter Open-Label Randomized Controlled Trial

**DOI:** 10.2196/89891

**Published:** 2026-06-02

**Keywords:** kanggan mixture, influenza, traditional Chinese medicine, randomized controlled trial, protocol

## Abstract

**Background:**

Influenza, a highly contagious acute respiratory illness, causes annual seasonal epidemics worldwide, imposing a substantial public health burden. Although neuraminidase inhibitors, such as oseltamivir, can shorten symptom duration, their use is limited by antiviral resistance and adverse reactions. Kanggan mixture (KGM), an in-hospital traditional Chinese medicine preparation at Jiangsu Province Hospital of Chinese Medicine, has been widely used in clinical practice for influenza treatment, showing favorable effects on fever reduction and symptom improvement; however, high-quality comparative evidence on the efficacy and safety of KGM remains limited. This study is designed to address this gap by evaluating whether KGM is noninferior to oseltamivir for the treatment of influenza.

**Objective:**

This study aims to determine whether KGM is noninferior to oseltamivir in improving the clinical outcomes in patients with influenza and to assess the safety profile of KGM.

**Methods:**

This study is a multicenter, open-label, randomized controlled trial to be conducted in 3 tertiary grade A hospitals in China. Eligible participants with influenza will be randomly assigned in a 1:1 ratio to receive either KGM or oseltamivir for 5 days. A total of 184 participants will be enrolled, with 92 (50%) participants in each group. The primary outcome is time to clinical alleviation. Secondary outcomes include time to defervescence, time to onset of antipyretic effect, individual influenza symptom scores, and total influenza symptom scores. Adverse events will be monitored throughout the trial to evaluate the safety of KGM.

**Results:**

This study was funded in July 2024. Recruitment began in September 2025 and is expected to be completed in June 2026. The study results are expected to be published by December 2026.

**Conclusions:**

This protocol describes a multicenter randomized controlled trial designed to generate comparative evidence on the efficacy and safety of KGM for influenza treatment. The findings of this study are expected to provide initial clinical evidence supporting the use of KGM in the treatment of influenza, clarify its therapeutic value as a potential alternative to oseltamivir, and offer a novel alternative strategy for influenza management while contributing to the evidence base for integrating traditional Chinese medicine into influenza care.

**Trial Registration:**

International Traditional Medicine Clinical Trial Registry ITMCTR2025000743; https://itmctr.ccebtcm.org.cn/mgt/project/view/-5368318132552339899

**International Registered Report Identifier (IRRID):**

DERR1-10.2196/89891

## Introduction

Influenza is a highly contagious acute respiratory illness caused by the influenza virus. Seasonal epidemics occur worldwide every year, and unpredictable pandemics can arise, imposing a substantial public health burden [1]. In China, approximately 3.4 million medical visits are attributable to influenza-like illness annually, with the mean economic cost per outpatient episode ranging from RMB ¥464 (US $65) to RMB ¥1320 (US $185, and an estimated 88,100 deaths per year are linked to influenza-associated respiratory disease, accounting for 8.2% of all respiratory disease mortality [2]. Notably, influenza is a leading cause of hospitalization for pulmonary respiratory diseases and remains a significant health burden for older individuals, neonates, and children [3-5].

Globally, oseltamivir, a neuraminidase inhibitor, is one of the most widely prescribed small-molecule antiviral agents against influenza. By blocking the release of progeny virions from infected cells, it curtails the replication of both influenza A and influenza B viruses and is approved for patients aged 1 year or older. A meta-analysis demonstrated that oseltamivir accelerates symptom alleviation and decreases the incidence of lower respiratory tract complications and hospitalization in adults [6]. Despite the widespread clinical application of oseltamivir, antiviral resistance and adverse reactions remain unresolved challenges [7,8]. Therefore, the development of effective and accessible countermeasures against influenza is a global priority.

Traditional Chinese medicine (TCM), with centuries of clinical antiviral experience, offers alternative strategies. The evidence suggests that combining TCM with oseltamivir shortens fever duration, hastens symptom resolution, and reduces the length of stay [9]. An open-label trial further revealed that TCM monotherapy for H1N1 influenza achieved a fever reduction equivalent to that of oseltamivir [10]. Kanggan mixture (KGM), a TCM widely used in clinical practice, is effective at dispersing wind heat, clearing heat, and resolving toxins. Over the past 2 decades, it has been widely used for the treatment of influenza in clinical practice, demonstrating consistent benefits for fever reduction and symptom improvement. KGM was originally an empirical prescription by [name], a famous Chinese medicine practitioner. It became an in-hospital preparation at Jiangsu Province Hospital of Chinese Medicine in 1998 and was approved by the Jiangsu Food and Drug Administration in 2006 (approval number Z20060004). The formula is composed of 12 botanical drugs, including honeysuckle, forsythia, mint, Platycodon, bitter almond, *Bistortae isatis root, Dryopteris crassirhizoma*, *Cimicifuga*, *Chizonepeta*, *Ligusticum chuanxiong*, and licorice. A previous study demonstrated that compared with the control, KGM had an efficacy rate of 96.67% for acute viral upper respiratory infection and reduced the time to defervescence [11].

However, high-level evidence of the efficacy of KGM in the treatment of influenza is lacking, and its safety profile requires systematic evaluation. Therefore, we designed this prospective, open-label, randomized, parallel-controlled, noninferiority trial to compare the efficacy and safety of KGM and oseltamivir in adults with influenza.

Therefore, we designed this prospective, multicenter, open-label, randomized, parallel-group, noninferiority trial to compare the efficacy and safety of KGM with those of oseltamivir in adults with influenza. We hypothesize that KGM is noninferior to oseltamivir in shortening the time to clinical alleviation and may improve influenza-related clinical outcomes with an acceptable safety profile.

## Methods

### Trial Design

The completed SPIRIT (Standard Protocol Items: Recommendations for Interventional Trials) checklist is provided in Multimedia Appendix 1. This protocol describes an open-label, randomized controlled trial that will be conducted in accordance with the SPIRIT 2025 statement [12]. Eligible participants will be randomly allocated (1:1) to receive either KGM or oseltamivir for 5 consecutive days [13]. This study is designed as an open-label trial. Given the characteristics of the interventions, blinding of participants and treating physicians is not feasible. To address the potential risk of performance and detection bias associated with the open-label design, outcome assessors and statisticians will be blinded to treatment allocation whenever feasible; if blinding cannot be implemented, standardized outcome definitions, validated scoring tools, investigator training, and quality control procedures will be applied to minimize potential bias. The study will be conducted at the Jiangsu Provincial Hospital of Chinese Medicine, Nantong Hospital of Traditional Chinese Medicine, and Yancheng Hospital of Traditional Chinese Medicine. All the investigators will complete a standardized training program at Jiangsu Provincial Hospital of Chinese Medicine before patient enrollment. This training will include the study protocol, eligibility assessment, end point definitions, symptom scoring methods, case report form completion, and sample collection, processing, and storage procedures. In addition, before study initiation, the study start-up requirements and related study documents have already been unified across all participating centers. Standard operating procedures and uniform case report forms will be used across all centers. Eligibility criteria, end point definitions, symptom scoring methods, and sample collection, processing, and storage procedures will be standardized. Throughout the study, regular coordination meetings, on-site or remote monitoring, data verification, and query resolution processes will be conducted to oversee protocol adherence across centers. In addition, centralized data review and regular cross-center communication will be conducted to further enhance consistency across sites. If inconsistencies or protocol deviations are identified, retraining and corrective actions will be undertaken promptly to improve data homogeneity and minimize intercenter variability. This study was approved by the ethics committee of the Affiliated Hospital of Nanjing University of Chinese Medicine (2025-NL-002-02) and was prospectively registered with the International Traditional Medicine Clinical Trial Registry (ITMCTR2025000743). An independent Data Monitoring Committee was not established, as the study was considered to involve minimal risk. No interim analysis is planned for this trial. Early termination of the study will only occur in the event of serious safety concerns or ethical issues, such as unexpected adverse events (AEs) or protocol violations that could compromise participant welfare. Efficacy results will not be used as a basis for stopping the trial early. To ensure participant safety, an independent safety oversight plan has been implemented, with the study monitored by the institutional ethics committee and independent reviewers who are not involved in participant recruitment, treatment delivery, or outcome assessment. AEs and serious adverse events (SAEs) will be collected, reviewed periodically, and reported promptly to the principal investigator and ethics committee. If safety concerns arise, recommendations for protocol modification, temporary suspension, or early termination of the trial will be made. A flow diagram of the study design is provided in Figure 1.

**Figure 1 figure1:**
[figure not shown]
Flowchart of participant screening, randomization, allocation to the Kanggan Mixture (KGM) and oseltamivir groups, and study completion.

### Sample Size

The sample size was determined based on the primary end point, namely the median time to the alleviation of influenza symptoms. Published studies have reported that the median time to symptom alleviation with oseltamivir is approximately 80 hours [14,15]. The assumption for KGM was informed by preliminary clinical evidence and prior clinical experience [11]. A noninferiority margin of 10 hours was prespecified with consideration of its clinical relevance and the feasibility of the trial. Under the assumptions of a 1:1 allocation ratio, a 2-sided significance level of .05, and 80% power, 78 evaluable participants were required per group. After accounting for an anticipated attrition rate of 15%, the target enrollment was set at 92 participants in each group, resulting in a total sample size of 184 participants.

### Recruitment

Participants will be recruited from 3 tertiary grade A hospitals in China. Recruitment strategies include screening outpatient and inpatient influenza cases, providing study information to potential participants via posters and hospital staff, and approaching eligible patients during routine clinical visits.

### Randomization and Allocation Concealment

Central stratified block randomization will be performed. All participant identifiers will be removed and replaced with study codes to ensure privacy protection. The allocation sequence was computer-generated via SAS 9.1 PROC PLAN (SAS Institute Inc) with a predefined seed. Sequentially numbered opaque sealed envelopes containing allocation codes will be centrally managed at each participating center.

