**Secondary outcome measurements**							
	Time to onset of antipyretic effect	✓		✓		✓	
	Duration of antipyretic effect	✓		✓		✓	
	Changes in viral load in nasopharyngeal secretions	✓				✓	
	Individual influenza symptom score	✓		✓		✓	
	Total influenza symptom score	✓		✓		✓	
	Changes in the traditional Chinese medicine syndrome score compared with baseline	✓				✓	

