#### Secondary Outcomes

The secondary outcomes are as follows:

Time to antipyretic onset: the interval from the first dose to the first documented decrease in axillary body temperature of at least 0.5 °C from baseline.Time to defervescence: time from the patient’s first dose until body temperature decreases to ≤37 °C and remains without recurrence for at least 24 hours.Changes in viral load in nasopharyngeal secretions: nasopharyngeal specimens will be collected at 2 predefined time points, day 0 (baseline) and day 5 (posttreatment), to evaluate changes in viral load over time. Viral load will be assessed using quantitative RT-PCR as a secondary virologic outcome to explore the effect of KGM on viral clearance.Individual influenza symptom scores: headache, fever or chills, myalgia, fatigue, cough, sore throat, and nasal congestion will each be scored on a 4-point ordinal scale ranging from 0 to 3, where 0 indicates absence of symptoms and 3 indicates severe symptoms.Total influenza symptom score: change from baseline and percentage change after dosing.

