### Statistical Methods

Study data will be entered into the electronic database independently by 2 trained research staff members, and discrepancies will be resolved by cross-checking to ensure accuracy. All data will be stored in a password-protected, access-restricted electronic database, with access limited to authorized study personnel.

Data management and analysis will be performed using SAS (version 9.4; SAS Institute) according to a prespecified statistical analysis plan. Statistical significance will be defined as a 2-sided *P* value of <.05, and 95% CIs will be reported.

Continuous variables will be summarized as mean (SD) for normally distributed data or median (IQR) for nonnormally distributed data. Categorical variables will be presented as frequencies and percentages. Normality will be assessed using the Shapiro-Wilk test, and the equality of variances will be examined using the Levene test. Between-group comparisons of continuous end point will be performed using an independent-sample 2-tailed *t* test (normal data) or the Mann-Whitney *U* test (nonnormal data). Categorical outcomes will be compared with the chi-square test or Fisher exact test, as appropriate. McNemar test will be performed to evaluate paired proportions when preintervention and postintervention data are available. All analyses will be conducted on both the full-analysis and per-protocol populations. For the primary outcome, missing data will be handled using multiple imputation, following current best practices, to reduce potential bias and improve the robustness of the findings. In addition, a sensitivity analysis will be performed using complete-case (listwise deletion) analysis to examine the consistency of the results under different missing-data assumptions.

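### Change-type secondary outcomes are compared without adjustment for baseline or randomisation strata, which gives up precision; the primary time outcome loses less, by an amount the article does not let one size

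*Protocol article*

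**What the plan says.** Under Randomization and Allocation Concealment the article states "Central stratified block randomization will be performed". It does not say which factors define the strata.

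Table 1 schedules the total symptom score at baseline, day 3 and day 5, and viral load and the TCM syndrome score at baseline and day 5. All three are framed as change:
- Secondary Outcomes: "Total influenza symptom score: change from baseline and percentage change after dosing".
- Secondary Outcomes, viral load: sampled on "day 0 (baseline) and day 5 (posttreatment), to evaluate changes in viral load over time".
- Table 1: "Changes in the traditional Chinese medicine syndrome score compared with baseline".

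Individual symptoms are defined only as 0 to 3 ordinal ratings, with no change analysis stated.

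Statistical Methods then fixes the tests: "Between-group comparisons of continuous end point will be performed using an independent-sample 2-tailed" t test for normal data, or a Mann-Whitney U test otherwise. For categorical data, "Categorical outcomes will be compared with the chi-square test or Fisher exact test, as appropriate". No stratum, centre or baseline term appears. The section also refers to a prespecified SAP, which is not shown.

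**The concern.** Two kinds of information that the trial already collects are left out of the comparison.

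First, subtracting the baseline value forces its coefficient to 1. Unless baseline predicts the later value that strongly, the subtraction adds baseline noise to the contrast. ANCOVA estimates the coefficient instead. Percentage change adds a further difficulty: the baseline value sits in the denominator, and the measure stops at -100% once a score reaches zero.

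Second, stratified allocation balances the arms on the strata. A test that omits them computes its standard error as if that balance had not been imposed, so the interval is wider than it needs to be.

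At stake is the precision of the supporting evidence on symptoms and viral load and, to a lesser and unknown degree, the width of the interval to be set against the 10-hour margin.

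**Working it through.** **The plan's own figure.** The article gives no number on this point. Its enrolment step reproduces (78/0.85 = 91.8, so 92 per group and 184 in total) and is not affected by what follows. I use 78 evaluable per group as n.

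**Inputs not in the article, therefore assumed.** Baseline-outcome correlation r of 0.2 to 0.6; share of outcome variance explained by strata or prognostic covariates, R², of 2% to 15%.

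**Change versus ANCOVA.** Take the post-baseline variance as 1 and let k be the ratio of baseline SD to post-baseline SD.
- Variance of change: 1 + k² - 2rk.
- Residual variance under ANCOVA: 1 - r².
- Difference: (k - r)², which is never negative.

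With equal SDs (k = 1) these become 2(1 - r) and 1 - r², so the standard-error ratio of ANCOVA to change is sqrt((1 + r)/2). That is below 1 for every r below 1, so the direction needs no assumed value. The 95% half-width in SD units is 1.96 × sqrt(2 × variance/78). The number per group that a change-score analysis needs to match ANCOVA with 78 is 78 × 2/(1 + r).

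| r | half-width, change | half-width, ANCOVA | narrower by | n per group to match |
|---|---|---|---|---|
| 0.2 | 0.397 | 0.308 | 22.5% | 130 |
| 0.4 | 0.344 | 0.288 | 16.3% | 112 |
| 0.6 | 0.281 | 0.251 | 10.6% | 98 |

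**Unequal SDs.** If scores fall toward zero as the illness resolves, the day-5 spread may be smaller than at baseline (k above 1) and the gap grows. A simulation with 78 per arm used an assumed scale (baseline mean 12, SD 3.5; day 5 mean 4, SD 3; values kept within the possible range). Half-widths for change versus ANCOVA were 1.17 versus 0.83 points at r = 0.3, 1.00 versus 0.76 at 0.5, and 0.79 versus 0.63 at 0.7, which is 29%, 24% and 20% narrower.

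**Chance imbalance.** With equal SDs, an observed baseline difference d moves the change contrast by (r - 1)d. One standard error of imbalance is sqrt(2/78) = 0.16 SD. At r = 0.4 it moves the contrast by 0.6 × 0.16 = 0.10 SD in size.

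**Strata and the primary outcome.** There is no baseline value of time to alleviation, so the formula above does not apply. What remains is the ratio sqrt(1 - R²), here an approximation borrowed from the linear case. If the strata carry the R² and are ignored, the true two-sided level of a nominal 5% test is 2 × (1 - Φ(1.96/sqrt(1 - R²))).

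| R² | adjusted interval narrower by | true level if strata ignored |
|---|---|---|
| 2% | 1.0% | 4.8% |
| 5% | 2.5% | 4.4% |
| 10% | 5.1% | 3.9% |
| 15% | 7.8% | 3.4% |

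**The case against.** The strongest reply is that covariates and model terms commonly belong in the SAP, which is not shown, and that an article's silence on them is no defect. That would dispose of a complaint about missing detail. Here, however, the article names the tests that will be used, and neither can carry a covariate or a stratum. A SAP that follows the article keeps the inefficiency; one that adds models departs from the published text. Either way the text needs attention.

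Several further objections stand and limit the point:
- A reader might infer that every between-group comparison is a t test or Mann-Whitney test. Categorical outcomes go to chi-square or Fisher tests (also unadjusted).
- A reader might take hospital to be the stratification factor. The article does not say so.
- A reader might carry the 11% to 23% over to the noninferiority decision. That range concerns secondary change outcomes, which have no margin; the 10-hour margin belongs to the primary time outcome.
- A reader might infer bias or an inflated error rate. Chance imbalance is random error already reflected in the standard error, and ignoring strata makes the test conservative, so false claims of noninferiority do not become more likely.
- The formula describes the t-test branch. A Mann-Whitney test yields no interval by itself, and its loss is not sized here.

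**Conclusion.** The point holds as one of efficiency. For total symptom score, viral load and TCM syndrome score, the stated unadjusted comparison of change is less precise than ANCOVA. The direction is algebraic; the size, about 11% to 23%, rests on equal SDs and assumed r of 0.6 to 0.2, and is larger if day-5 spread is smaller than baseline spread. For the primary outcome the gain is probably small: 1% to 8% under assumed R² of 2% to 15%, with nothing in the article to narrow that range. The point shows no error in the sample size and no threat to validity.

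**What to change.** In Statistical Methods and the SAP:
- Analyse the total symptom score, log10 viral load and TCM syndrome score by ANCOVA, or by a repeated-measures model where there are several visits. Use the post-baseline value as the response, with its baseline value and the randomisation strata as covariates.
- Keep percentage change as a descriptive summary, without a test.
- Individual 0 to 3 items may keep a rank or ordinal method, adjusted for strata and baseline.
- Analyse the primary outcome by a method that accounts for the strata and still gives a difference in hours, for example a stratum-weighted Kaplan-Meier contrast. A stratified Cox model is not a substitute, because a hazard ratio cannot be set against a margin of 10 hours.

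The cost is wording. The baseline measurements are already scheduled and the strata are known from the randomisation. As the trial is open-label and recruitment is due to end in June 2026, the change should be dated and recorded as an amendment before anyone sees outcome data by arm.

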### TCM Syndrome Differentiation

According to the 2016 Technical Guidelines for Clinical Research on TCM New Drugs for Influenza, wind heat invading the defensive *qi* is diagnosed when a patient presents with at least 2 major and 2 minor symptoms together with specified tongue and pulse findings.

The major symptoms include fever and sore throat. The minor symptoms include cough, nasal congestion or rhinorrhea, thirst, headache, myalgia, fatigue, and aversion to wind. Tongue and pulse findings include a red tongue body with a thin yellow or white coating and a floating and rapid pulse.

